#### Adherence

Adherence monitoring will be performed to find new strategies to avoid attrition during the study and to look for unexpected problems that may prevent patients from attending the sessions. Patients will receive weekly phone calls to confirm appointments and obtain educational instructions about the study protocols to reassure them of the importance of adherence. Upon discharge, patients will be provided with instructions to contact their physician for unacceptable levels of sleep disability or perceived stress to receive an outpatient prescription of antianxiety medications and lifestyle techniques. Additionally, if a patient deviates from the intervention protocol assigned to them, they will not be considered a study failure. Instead, we will continue to follow the patient through study completion and continue to track patient-reported outcomes.

### Data Collection and Outcome Measures

#### Baseline Assessments and Frequency of Follow-Up Assessments

A full list of assessments obtained at each time point is summarized in Table 3.

We will obtain baseline assessments during each patient’s screening visit. These measures will include, but will be not limited to, demographics, comorbidities, subjective sleep quality and perceived stress rating, ophthalmic and laboratory outcomes, and patient-reported outcomes specific to the planned intervention.

Initial follow-up assessments will be obtained at 1, 2, 3, and 4 weeks after the start of the intervention. Patients will also be asked to return for postintervention follow-up visits 6 months after the intervention. These visits will be scheduled at the beginning of the study. Patients unable to attend any in-person visit will be asked to at least provide all subjective patient-reported outcomes over the phone or via an electronic survey for that visit in order to facilitate retention and optimal follow-up.

Sleep quality level, laboratory outcomes, ophthalmic clinical outcomes, questionnaire patient-reported outcomes, and potential complications will be gathered during these visits.

**Table 3 table3:** Assessments and follow-up.

Clinical and laboratory event	V_–1_^a^ (–4 weeks)	V_0_ (0 weeks)	V_1_ (1 weeks)	V_2_ (2 weeks)	V_3_ (3 weeks)	V_4_ (4 weeks)	V_F_ (6 months)
Screening	✓^b^	—^c^	—	—	—	—	—
Clinical	—	✓	—	—	—	✓	✓
Physical examination	—	✓	—	—	—	✓	✓
Salivary sample collection	—	✓	✓	✓	✓	✓	—
Hair sample collection	—	✓	—	—	—	✓	—
STAI^d^ questionnaire	—	✓	—	—	—	✓	—
ESS^e^ and PSQI^f^ questionnaires	—	✓	—	—	—	✓	—
Inclusion criteria	✓	—	—	—	—	—	—

^a^V: visit; V_–1_, screening visit, when inclusion and exclusion criteria will be checked; V_0_, visit to assess baseline characteristics; V_1_-V_4_, visits during the intervention period (every week); and V_F_, final visit after 6-month follow-up.

^b^✓: applicable.

^c^Not applicable.

^d^STAI: State-Trait Anxiety Inventory.

^e^ESS: Epworth Sleepiness Scale.

^f^PSQI: Pittsburgh Sleep Quality Index.

#### Primary Outcome Measures

The primary outcomes are the differences in changes from baseline to postintervention in hormone release (sAA, cortisol, and melatonin levels in salivary and hair samples) and sleep quality, as measured by the ESS and the PSQI.

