A draft intervention protocol will be developed for each group, covering preintervention, intervention, postintervention, and discharge settings based on the literature. A steering committee comprising ophthalmologists, opticians, nurses, psychologists, and the research team will be created to develop these protocols. Additionally, 2 ophthalmology residents will be included. Finally, 1 patient with RP, who is the current president of the Federation of Inherited Retinal Dystrophies’ Associations, will be included in the steering committee. The steering committee members are experts in their respective fields and have used the existing literature (summarized in the *Background and Rationale* section) to inform the inclusion of the different interventions in the protocols. The draft intervention protocols are presented in Table 1. Although the choice of each intervention in these protocols will be informed by the literature [7,28,30,36,51,57,67,75-82] and expert consensus of the steering committee, the study will assess the efficacy of combined interventions in sleep disorders and stress control in a large group of patients with RP. Before the intervention period, all patients will be asked to complete sleep diaries for 2 weeks. In addition, patients in the intervention groups (SWL, OM, SWL+OM) must complete them during the intervention period (30 days). Patients from the SWL and SWL+OM groups will wear SWL-restricting goggles in bright-light conditions and when using light-emitting diode (LED) electronic devices for the 30 days of intervention. Patients from the OM and SWL+OM groups will take 3 pills of Circadin 2 mg (OM) every evening at 10:00 P.M. with a margin of 30 minutes before and after.

A preintervention time of 1.5 years will be necessary for recruitment, informed consent, eligibility screening, and baseline data collection. Next, patients will be randomized to 4 groups in a 1:1 ratio. The treatment groups will include SWL with or without the use of OM. The control group will include patients who are eligible for the study but not willing to be randomized to an intervention sleep and stress management pathway. When the intervention phase (4 weeks) is over, all patients will be followed up for 6 months via standard monitoring. Figure 2 provides a summary of the RCT timeline.

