##### Salivary α-Amylase, Cortisol, and Melatonin levels

Salivary samples will be collected by patients using the passive secretion drooling method. Two samples of saliva from each patient will be collected in 24 hours. At least 1 mL is required for analysis. The putative salivary indicators will be assayed with enzyme-linked immunosorbent assay (ELISA): cortisol (DRG Salivary Cortisol ELISA, DRG Instruments GmbH) and melatonin (DRG Instruments GmbH). Salivary α-amylase (sAA) will be determined with an α-amylase kit (Salimetrics) [93].

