#### Oral Melatonin (6 mg)

Patients will be asked to intake a 6 mg melatonin dose orally once a day for 30 days in the evening (22:00 P.M. with a margin of 30 minutes before and after) to activate its sleep-promoting effects approximately 2 hours after intake, avoiding fatigue and sleepiness during the daytime [96-99].

Although the chosen dose is safe to obtain the desired effect, patients will be prompted to report any possible side effects, if present, during the intervention period [79,81,82,100]. If they experience unbearable side effects, they will have to discontinue the OM intervention. If they wish, they can participate in the SWL-blocking intervention and will be evaluated over the 4-week follow-up period.

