#### SWL Blocking + Oral Melatonin (6 mg)

Participants in this combination arm will receive both interventions—filter goggles and OM—at the same time under the same conditions as the SWL and OM groups and for the same 30-day period.

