#### Statistics

A linear mixed effect regression model will be applied to compare intervention arms against the control at baseline and stimulated measures for the HPA axis or the retinal–SCN–pineal axis comprising cortisol, melatonin, and sAA [106]. Baseline characteristics of patients from each group will be compared applying independent *t* tests, 2-way repeated-measures ANOVA, and the Fisher exact test. To grade the RP severity (by quantifying clinical features, the ETDRS score, and visual field deviation) and the primary outcomes, we will consider both to be continuous variables and apply a multiple linear regression model. For secondary outcomes, normally distributed variables will be statistically assessed via parametric tests, such as the *t* test or ANOVA, while nonnormal distributed variables will be assessed with nonparametric tests, such as the chi-square test or the Fisher exact test and the Mann–Whitney U test. A chi-square or Fisher test will be performed to compare STAI, PSQI, and ESS scores among groups.

Statistical associations between covariates and outcomes will be evaluated using the appropriate statistical methodology, as previously described. Multivariable linear regression models will be appropriately fitted to continuous data based on the distributions of those data. Multiple logistic regression models will be fitted for all dichotomous outcome variables. Appropriate variable selection methods and model fit statistics will be used to determine the best-fitting model to determine the effects of treatment after adjusting for significant effects of covariates.

Finally, any protocol amendment will be first submitted to the Institutional Review Board for approval. If the amendment changes anything about what is reported

on ClinicalTrials, then the study’s registration on ClinicalTrials will be updated accordingly.

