In addition to its pleiotropic actions, melatonin possesses an advantage over other possible candidates due to its amphiphilic character, which enables it to enter any fluid, cells, or subcellular structures, including mitochondria. Conversely, melatonin exhibits poor pharmacokinetic properties (eg, limited oral bioavailability and short plasma half-life) and low subtype receptor selectivity [79,81]. The effective doses reported are between 0.5 and 10 mg without a clear dose-response relationship (Multimedia Appendix 1). This mainly reflects the large interindividual variability in melatonin bioavailability, which is well known in the published literature and is attributed to differences in first-pass metabolism (Multimedia Appendix 1).

The acute toxicity of melatonin, as seen in both animal and human studies, is extremely low [82]. Melatonin may cause minor adverse effects, such as headache, insomnia, rash, diarrhea, and nightmares [82]. In animals, a lethal dose for 50% of the subjects (LD50) could not be established; even 800 mg/kg body weight (high dose) was not lethal [100]. Studies on human subjects given varying doses of melatonin (1-6.6 g/day) for 30-45 days and followed with an elaborate battery of biochemical tests to detect potential toxicity have concluded that in addition to drowsiness, all findings were normal at the end of the test period [79,81,82].

In the same line as the previous Spanish RCT (EudraCT no: 2012-002436-82) with OM and patients with RP, we have considered that 6 mg of OM for 30-40 days will be a safe dose to reach the desired effects without causing side effects in our target population. In general, a dose between 0.2 and 10 mg has been considered a safe starting dose in most of the previous studies with OM [67,79,81,82].

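### In comparisons of a melatonin arm with a non-melatonin arm, the primary salivary melatonin outcome cannot separate ingested from endogenous hormone

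*Protocol article*

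**What the plan says.** **Outcome.** Primary Outcome Measures lists change from baseline to postintervention in "hormone release (sAA, cortisol, and melatonin levels in salivary and hair samples", together with ESS and PSQI. Only saliva has a described melatonin assay, an ELISA. The hair assay is for cortisol.

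**Analysis.** Statistics plans a linear mixed model to "compare intervention arms against the control at baseline and stimulated measures for the HPA axis or the retinal–SCN–pineal axis comprising cortisol, melatonin, and sAA". It has no separate provision for the arms that take melatonin.

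**Study drug.** Under Oral Melatonin (6 mg): "Patients will be asked to intake a 6 mg melatonin dose orally once a day for 30 days in the evening". The Methods overview says that OM and SWL+OM patients "will take 3 pills of Circadin 2 mg (OM) every evening at 10:00 P.M", with 30 minutes' leeway either way. For SWL+OM: "Participants in this combination arm will receive both interventions", under the same conditions and for the same 30 days.

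**Sampling.** Table 3 marks saliva at V0 and at V1 to V4, described as "visits during the intervention period (every week", and leaves the 6-month visit blank. Laboratory Assessment sets collection between 9:00 and noon, and gives diurnal variation as the reason. The salivary section adds: "Two samples of saliva from each patient will be collected in 24 hours". It gives no clock time for either sample.

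**Background.** The Discussion describes oral melatonin's plasma half-life as short without giving a figure, refers to "large interindividual variability in melatonin bioavailability", and calls daytime endogenous levels minimal.

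**The concern.** The substance measured as hormone release is also the substance given in two arms. Nothing described for the assay distinguishes a molecule from the tablet from one made by the patient. If drug is still present at sampling, OM or SWL+OM can exceed control on a primary outcome without any change in the axis that the outcome is meant to represent. The same ambiguity affects OM versus SWL and SWL+OM versus SWL. Two of the three intervention-versus-control contrasts that the model is built to give are affected, and four of the six possible pairwise contrasts.

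**Working it through.** **1. Are the post-baseline samples on drug?**
V1 to V4 fall at weeks 1, 2, 3 and 4, that is days 7, 14, 21 and 28. Dosing runs for 30 days. So 4 of 4 post-baseline saliva visits are on drug and 0 are off drug. If the course is read as 4 weeks, as some sections have it, V4 still falls at the end of dosing.

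**2. How long after the dose?**
The dose is taken between 21:30 and 22:30, and the sample between 9:00 and 12:00.
- Shortest gap: 22:30 to 9:00 = 10.5 h.
- Longest gap: 21:30 to 12:00 = 14.5 h.

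This assumes that the window, which is stated in the screening material, also governs V1 to V4.

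**3. How much drug could remain?**
With first-order decline from the time of dosing, the remaining fraction is 2^(−t/h), where t is the gap and h the half-life. The documents give no h, so the values below are assumptions.

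| Assumed half-life | At 10.5 h | At 14.5 h |
|---|---|---|
| 1 h | 2^(−10.5) = 0.069% | 2^(−14.5) = 0.0043% |
| 2 h | 2^(−5.25) = 2.6% | 2^(−7.25) = 0.66% |
| 4 h | 2^(−2.625) = 16% | 2^(−3.625) = 8.1% |

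The formula treats absorption as immediate. Slower absorption would leave more.

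**4. Is that large against the patient's own daytime level?**
This needs the ratio of the post-dose peak to the daytime endogenous level, which the documents do not give. Purely for illustration, assume 100 to 1,000. Carry-over as a multiple of the daytime level is then the fraction times the ratio:
- 1 h: 0.000043 × 100 = 0.004 up to 0.00069 × 1,000 = 0.69.
- 2 h: 0.0066 × 100 = 0.66 up to 0.026 × 1,000 = 26.
- 4 h: 0.081 × 100 = 8.1 up to 0.16 × 1,000 = 160.

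The answer runs from negligible to dominant, and the plan contains nothing that settles where it lies.

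**5. Which contrasts are affected?**

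| Contrast | Assigned melatonin intake | Drug and endogenous hormone confounded? |
|---|---|---|
| SWL vs control | none / none | No |
| SWL+OM vs OM | 6 mg / 6 mg | No, but noisier |
| OM vs control | 6 mg / none | Yes |
| SWL+OM vs control | 6 mg / none | Yes |
| OM vs SWL | 6 mg / none | Yes |
| SWL+OM vs SWL | 6 mg / none | Yes |

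At 15 patients per group, the two melatonin arms hold 30 of 60 patients.

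**The case against.** **The morning window may be enough.** Samples at 9:00 to noon are far from the dose, and the half-life is called short. At about 1 hour the residue is very small. A reader might infer that values in the melatonin arms simply are the study drug. The documents do not support that: they show that drug and hormone cannot be told apart, not that drug predominates. Nor does a negligible residue rescue the reading as hormone release, because a sample taken when endogenous levels are minimal says little about night-time secretion.

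**No night sample is scheduled.** A reader might infer from two samples in 24 hours that one is taken near the dose. Read with the 9:00-to-noon window, both could be morning samples. The unstated times are an ambiguity and no more.

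**An off-drug sample may be intended.** The text above Table 3 says that laboratory outcomes are gathered at visits that include 6 months, and the outcome refers to postintervention. Table 3 nevertheless schedules no saliva then. A 6-month sample would in any case not show the effect during treatment.

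**Melatonin alone need not decide the trial.** A reader might infer that a primary success could be declared on tablet intake. No rule says that one primary outcome suffices, so this does not follow.

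**The combination can still be studied.** A reader might infer that any added effect of the filters on top of melatonin is unreadable on this outcome. SWL+OM versus OM has the same dosing in both arms, so the dose adds variability without by itself biasing the contrast. The cited variability concerns bioavailability between people, and its size 10 to 14 hours later is not given.

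These points narrow the concern. None of them repairs a comparison of a dosed arm with an undosed one.

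**Conclusion.** The point holds for contrasts with unequal melatonin intake. In OM or SWL+OM versus control or SWL, the plan labels as hormone release a quantity in which ingested and endogenous melatonin cannot be separated, and a difference may show only tablet intake. This rests on the documents' own schedule: 4 of 4 post-baseline saliva visits during dosing, in 2 of 4 arms. The size of the carry-over is unknown. The range of about 0.004% to 16% of peak rests on assumed half-lives of 1 to 4 hours and on the morning window applying at every visit. SWL versus control is free of the problem, and SWL+OM versus OM is less precise but not invalidated. Cortisol, sAA, ESS and PSQI are not the ingested substance and are unaffected by this point. Because a named primary outcome is involved and the trial has not started, it should be corrected before launch.

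**What to change.** In Primary Outcome Measures and Statistics:

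1. Restrict salivary melatonin as an efficacy outcome to contrasts with equal assigned melatonin intake: SWL versus control as the main one, and SWL+OM versus OM as supportive, acknowledging the added between-patient variability from the dose.
2. Report OM or SWL+OM versus control or SWL as exposure and adherence only, and state that it will not be read as an effect on hormone release.
3. Keep cortisol, sAA, ESS and PSQI as outcomes for all four arms.

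While editing, state the clock times of the two saliva samples and reconcile the 6-month text with Table 3.

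The cost is rewording, with no new visits or assays. The downside is one fewer primary endpoint on which the melatonin arms are compared with control. The change removes the confounding with the dose. It does not make a morning sample informative about night-time release, so the retained contrasts should be described as morning salivary levels.

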**Methods:**

We have developed a low-cost therapy protocol for patients with RP with sleep disorders and negative psychological stress. Patients will be randomized to receive a combined intervention with SWL-blocking filters and OM, SWL-blocking filters alone, or OM alone. There will also be a nonintervention arm as a control group. This study will be conducted across 2 retinal units in patients with RP with sleep disorders and high perceived stress and anxiety score reports. Patients will be assessed in the preintervention period, weekly during the 4 weeks of intervention, and then at 6 months postintervention. The primary outcomes are the differences in changes from baseline to postintervention in hormone release (α-amylase, cortisol, and melatonin) and sleep quality, as measured with the visual analog scale. Secondary outcome measures include clinical macular changes, as measured with optical coherence tomography and optical coherence tomography angiography; retinal function, as measured using the visual field and best-corrected visual acuity; sleep data collected from personal wearables; and several patient-reported variables, such as self-recorded sleep diaries, quality of life, perceived stress, and functional status.

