### Statistical Analysis

#### Sample Size Calculation

A sample size estimation of 48 patients (n=12, 25%, per group) was calculated for a target power of 80% and considering an α (probability of rejecting a true null hypothesis) of 5% and an actual power of 80.02%. Cohen d was 1.2 [101]. Due to the possible overestimation of the effect size in pilot studies, an effect size of 0.6 (medium-high) was chosen for this study. We calculated a total sample size of 60 participants (a total of 15, 25%, patients per group), adding approximately 20% (3 more patients per group than before) to manage possible dropouts [102-105].

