#### Missing Data

Dropouts and missing facts are known as missing data. A dropout rate of 5%-10% is expected based on recent OM clinical trials [99,107]. An intention-to-treat analysis, regardless of the treatment administered, will be carried out for every primary and secondary endpoint. A preprotocol analysis will also be conducted with those who complete the trial, since secondary outcomes could be more affected by uncensored withdrawals. Both analyses must be favorable for the intervention to be considered better than standard. To deal with missing data, imputation techniques will be applied.

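### The primary sleep outcome is a visual analog scale in the Abstract but the ESS and PSQI in the Methods, and six unranked primary endpoints sit on a sample size for one unadjusted comparison

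*Protocol article*

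**What the plan says.** **Sleep instrument.** The Abstract (Methods) gives the primary outcomes as changes in hormones "and sleep quality, as measured with the visual analog scale". Primary Outcome Measures gives "hormone release (sAA, cortisol, and melatonin levels in salivary and hair samples) and sleep quality, as measured by the ESS and the PSQI". The questionnaire sections describe the STAI, ESS, PSQI and a sleep diary. Table 3 schedules the STAI, ESS and PSQI at baseline and week 4. Neither place contains a visual analog scale.

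**Primary endpoints.** Three salivary analytes are assayed (sAA, cortisol, melatonin). Cortisol is the only analyte named for hair. No endpoint is ranked above another.

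**Comparisons.** Statistics uses a linear mixed model to compare the intervention arms with control on the hormones. ESS and PSQI scores are compared among groups by chi-square or Fisher test.

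**Sample size.** "A sample size estimation of 48 patients (n=12, 25%, per group) was calculated for a target power of 80"%, at a 5% alpha and an actual power of 80.02%. Two effect sizes follow: "Cohen d was 1.2", and then "an effect size of 0.6 (medium-high) was chosen for this study". The total is raised to 60 for dropout.

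**Success rule.** Under Missing Data, with reference to the intention-to-treat and completer analyses: "Both analyses must be favorable for the intervention to be considered better than standard".

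**The concern.** There are two linked problems.

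First, the primary sleep instrument differs between Abstract and Methods, and the one in the Abstract cannot be obtained from the schedule. The trial is not yet registered, so the contradiction can still be removed before a registry entry is written from either text.

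Second, the protocol fixes several co-equal primary endpoints and three active arms, but sizes the trial as if there were a single comparison. Its success rule says that two analysis sets must agree. It does not say on which endpoint, for which arm, or on how many. A reader of the results could not tell from the protocol whether one favorable hormone in one arm is a success or whether everything must succeed. Those readings carry very different false-positive risks and very different power.

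**Working it through.** **1. Count of endpoints and tests.** Salivary analytes 3 + hair cortisol 1 + ESS + PSQI = 6 endpoints. Three arms against control give 6 × 3 = 18 tests. If ESS and PSQI each get one among-groups test, as Statistics can be read, the count is 4 × 3 + 2 = 14.

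**2. The plan's own sample size.** Two-sample t test, noncentral t distribution, two-sided α = 0.05, d = 1.2, n = 12 per group: power 80.2%, against the stated 80.02%. The required n is 11.94, so 12 per group and 4 × 12 = 48. Dropout: 48 / 0.8 = 60. Both figures reproduce with no division of alpha.

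The second stated effect size does not lead to 48. Read as Cohen d, 0.6 gives 29.0% power at n = 12 and 35.5% at n = 15. Read as Cohen f in a four-group ANOVA, a total of 36 already gives 82.1%. Of the stated effect sizes, only d = 1.2 in one unadjusted comparison yields the stated n.

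**3. False-positive risk if any one test sufficed.** Under full independence, either direction: 1 − 0.95^18 = 60.3% for 18 tests and 1 − 0.95^14 = 51.2% for 14.

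The arms share one control group, so the 18 tests are not independent. A simulation under no effect anywhere allows for this: four arms of 12, six normal endpoints with equal correlation ρ, t tests against control at two-sided 5%, 40,000 runs. The protocol gives no ρ, so a range is shown.

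| ρ | at least one significant, favorable direction | at least one significant, either direction |
|---|---|---|
| 0 | 32.4% | 56.0% |
| 0.3 | 27.5% | 51.8% |
| 0.5 | 23.9% | 45.6% |
| 0.7 | 19.3% | 37.8% |

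With one endpoint and three comparisons, still unadjusted, the figures are 6.3% (favorable) and 12.5% (either direction).

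**4. Power under adjustment.** Two-sample t test, n = 12 per group, at the strictest (first) Holm step, reading 0.6 as Cohen d:

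| Family | first-step α | d = 1.2 | d = 0.6 |
|---|---|---|---|
| none | 0.05 | 80.2% | 29.0% |
| 1 endpoint × 3 arms | 0.05/3 = 0.0167 | 63.8% | 15.4% |
| 6 endpoints × 3 arms | 0.05/18 = 0.0028 | 36.5% | 4.8% |

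At d = 1.2, 80% power at 0.05/18 would need 23 per group.

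**The case against.** A reader might infer that all 18 tests are to be run at 5% each and that a false claim of success is therefore about as likely as not. The document does not support either step.

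- **Each test at 5%.** The only alpha stands in the sample size paragraph and describes the power calculation. Statistics gives no level for the primary tests. An article may leave the multiplicity procedure to an analysis plan that is not shown, so its absence is no finding.
- **About as likely as not.** That figure counts significance in either direction. The success rule asks for favorable results, which brings it to roughly 24% to 32%, and requiring both analysis sets to agree lowers it a little further. For the hormones the protocol defines no favorable direction, so the either-direction figure keeps some relevance, but it is not the risk of a false success claim.
- **Any endpoint suffices.** The protocol does not say so. If every endpoint had to succeed, there would be no inflation at all.

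The visual analog scale can also be called an isolated slip in the Abstract, since the operative sections use the ESS and PSQI throughout. That is fair as to its origin, but it remains a contradiction on a primary outcome.

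The Conclusions of the Abstract call this a feasibility trial, which lowers the stakes. However, the Background states an efficacy aim, Missing Data sets a rule for calling the intervention better, and the Conclusion looks ahead to superiority.

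What stands is what the protocol itself fixes: two different sleep instruments, six unranked primaries, a sample size with no allowance for them, and a success rule with no endpoint. A later analysis plan could add an adjustment, but it could not restore the power that 12 per group lacks.

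**Conclusion.** The point holds in this limited form. The contradiction on the sleep instrument is textual and certain. The unranked primaries and the single-comparison sample size are also in the text, the latter confirmed by reproducing 12 per group.

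The size of the error is conditional. It assumes that one significant test is enough, that each is run at an unadjusted two-sided 5%, that all six endpoints are compared arm by arm with control, and that endpoint correlation lies between 0 and 0.5. On those terms the favorable-direction risk is several times 5%, though below one in two. Counting 14 tests instead of 18 does not change the conclusion. Three comparisons is the smaller count, because the Background also sets the combination against each single intervention.

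**What to change.** Before registration:

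1. Replace the visual analog scale in the Abstract with the instruments named in Primary Outcome Measures, and use the same wording in the registry entry.
2. Have the sponsor name one primary endpoint and make the others secondary. Change in global PSQI to week 4 is one option: its one-month recall matches the intervention, and Table 3 collects it at baseline and week 4. A hormone is another, and the choice is the sponsor's. If PSQI is chosen, the among-groups chi-square or Fisher comparison must become an arm-versus-control comparison of change.
3. Apply Holm at a familywise 5% over the three arm-versus-control comparisons.
4. Tie the success rule under Missing Data to that endpoint and to the arms that pass Holm.
5. Restate the power at the adjusted level and for the effect size actually adopted.

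The first four are changes of wording. The real cost is power, which drops to 64% (d = 1.2) or 15% (d = 0.6) at the first Holm step with 12 per group, so the sponsor must either accept lower power or revisit the sample size. Keeping all six endpoints primary with Holm over 18 is not recommended, since about 36% (d = 1.2) or 5% (d = 0.6) would remain at the first step.
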